## Methods

### Trial design {8}

This study is a randomized-controlled parallel-group trial examining the effect of a short, animated storytelling video on knowledge and behavioral expectation to reduce dietary sodium intake. We will use an online academic research platform (Prolific Academic) to recruit and randomize 10,000 participants aged 18–59 years into four study groups.

In group 1 (intervention group), participants will be shown a SAS video on dietary sodium (see multimedia Appendix) and thereafter be asked to complete a questionnaire to assess knowledge on dietary sodium and behavioral expectation.

In group 2 (exposed control group), participants will be asked to complete a questionnaire to assess knowledge on dietary sodium and behavioral expectation (the same questionnaire as in group 1), however, without being exposed to the SAS video on dietary sodium before.

In group 3 (attention placebo control group), participants will be shown an attention placebo control (APC) video, unrelated to the outcomes measured in this trial, before being asked to complete the knowledge and behavioral expectation questionnaire.

Participants in group 4 (unexposed control group) will not view a video and will not be asked to complete the questionnaire.

Two weeks later, participants in all four arms will once again be asked to complete the knowledge and behavioral expectation questionnaire. Figure 1 illustrates the trial design.

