### Explanation for the choice of comparators {6b}

At time point 1, knowledge scores and behavioral expectation will be compared between three groups that will receive the questionnaires (*Intervention Arm – Do-nothing Exposed Arm – Attention Placebo Arm*). This comparison is intended to find out the immediate effect on knowledge and behavioral expectation about sodium intake by watching the intervention video. The primary comparison will be between the *Intervention Arm* and the *Do-nothing Exposed Arm.* By comparing these groups with the *Attention Placebo Arm* we will also be able to eliminate a potential generalized attention-activation effect from watching an animated short film (unrelated to sodium).

At time point 2, comparing the *Intervention Arm* with the *Do-nothing Un-exposed Arm* will allow us to detect potential medium-term effects of watching the intervention video on knowledge and behavioral expectation — participants in the *Do-nothing Un-exposed Arm* will neither have been exposed to the intervention video nor the sodium knowledge questions at time point 1. At time point 2, comparing the *Do-nothing Exposed Arm* with the *Do-nothing Un-exposed Arm* will provide information about the effect of simply asking sodium-related questions on medium-term knowledge and behavioral expectation to reduce dietary sodium.

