### Recruitment and strategies to improve adherence to interventions, promote participant retention, and complete follow-up {15, 11c, 18b}

Adequate participant enrolment to reach the target sample size will be guaranteed by Prolific Acedemic (ProA). ProA has a sufficiently large database of registered prospective trial participants.

The major strategy to improve adherence to the interventions in this trial is to offer payment to all participants. The payments will be given only after completing the whole survey (i.e., once the medium-term follow-up questionnaire is finished). If participants spend more than 45 min on any phase of the trial, they will be timed out of the experiment. This prevents participants from burdening the system with partially completed questionnaires. Throughout the study, investigators will have no access to the identity of the participants, so follow-up with individual participants is not possible. All incomplete datasets from participants who discontinue or deviate from intervention protocols will be descriptively reported.

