### Criteria for discontinuing or modifying allocated interventions {11b}

Participants may withdraw their consent to participate in the study at any time before or during the study. Data from incomplete surveys will not be used in the primary analysis, except at a meta-level to report the aggregate number of incomplete surveys.

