#### Primary outcomes

For each participant, the overall score achieved in the sodium questionnaire will be calculated individually. The mean score for each study arm at time point 1 and time point 2 (i.e., re-assessment 14 days after entering the trial) will be calculated and compared between the *Intervention Arm*, the *Attention Placebo Arm*, and the *Do-nothing Exposed Arm* at time point 1 and between all four study groups at time point 2, using the *t*-test for two independent groups. We will also use multilevel regression analyses to control for demographic factors and other potential variables as needed. The analyses will be conducted using the R statistical software package (R 4.2.2).

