### Methods in analysis to handle protocol non-adherence and any statistical methods to handle missing data {20c}

Participants in the study will have a time limit of 45 min to watch the short, animated storytelling videos and answer the questionnaires. All items of each questionnaire are designed such that all questions have to be answered before the questionnaire can be submitted. This will guarantee that there will no missing values in the datasets of participants included in the analyses. All participants who have participated and completed the first round of the study (time point 1) will be included in the study of medium-term effect (time point 2, 14 days later). If a participant, who submitted a completed survey at time point 1, fails to complete a survey at time point 2, their data will only be included in the immediate effect analysis. Participants who do not watch the videos or answer the questionnaire items at either time point will be excluded from the analysis.

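### Excluding participants who do not watch the video can act only in the two video arms, and so may bias the primary comparison, most likely in favour of the video

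*Protocol article*

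**What the plan says.** Section {20c} of the protocol article, on non-adherence and missing data, ends with the rule "Participants who do not watch the videos or answer the questionnaire items at either time point will be excluded from the analysis". The sentence just before it keeps a participant who completes time point 1 but misses time point 2 in the immediate-effect analysis.

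Only two arms have a video at time point 1 (Trial design {8} and Table 1): the Intervention Arm and the Attention Placebo Arm. The Do-nothing Exposed Arm answers the questionnaire "without being exposed to the SAS video on dietary sodium before". For the fourth arm, "Participants in group 4 (unexposed control group) will not view a video and will not be asked to complete the questionnaire".

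Section {6b} names Intervention versus Do-nothing Exposed as the primary comparison at time point 1, and uses Intervention versus Do-nothing Un-exposed for the medium-term effect. The section on primary outcomes compares means "using the *t*-test for two independent groups".

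Two other sections touch on exclusions. Section {11b} says "Data from incomplete surveys will not be used in the primary analysis, except at a meta-level to report the aggregate number of incomplete surveys", and section {15, 11c, 18b} says "All incomplete datasets from participants who discontinue or deviate from intervention protocols will be descriptively reported". Neither says that participants are analysed as randomised regardless of adherence, and no other section does.

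**The concern.** Watching happens after randomisation, and only two arms have anything to watch. An inattentive person in the Intervention Arm who skips the video and submits the questionnaire would be removed. An equally inattentive person in the Exposed Arm who submits the questionnaire would stay. The t-test would then compare watchers with all completers, and randomisation no longer makes those two groups alike. At time point 2 the imbalance is wider, because the Un-exposed Arm passes neither a video nor a questionnaire filter at time point 1.

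The planned regression adjusts for demographic factors, which need not capture attentiveness. The target effect is only d=0.1, so even modest selection could be a sizeable part of what the trial is built to detect.

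**Working it through.** **The plan's own figure.** Inputs from section {14}: d=0.1, one-tailed error 0.01, power 80%. Then n = 2(2.326 + 0.842)² / 0.1² ≈ 2008 per arm, against 2009 stated. The figure reproduces, so the trial is indeed sized for a 0.1 SD difference. Recruitment is 2500 per arm.

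**Bias from the filter with no true effect.** Let p be the share of the video arm that does not watch, and δ the amount in SD by which non-watchers would score below watchers in any arm. The documents give neither, so both are assumptions. If watchers have mean μ, a whole arm has mean μ − pδ. Dropping non-watchers on one side only gives a difference of μ − (μ − pδ) = pδ.

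With total variance 1, the variance among watchers is v = 1 − p(1−p)δ². The standard error is SE = √[1/2500 + v/(2500(1−p))], and the one-sided error is Φ(pδ/SE − 2.326).

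For p=5%, δ=0.5: pδ = 0.025, v = 0.988, SE = √(1/2500 + 0.988/2375) = 0.0286, and Φ(0.875 − 2.326) = 7.3%.

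| p | δ | Bias (SD) | Share of d=0.1 | Error (nominal 1%) |
|---|---|---|---|---|
| 2% | 0.25 | 0.005 | 5% | 1.6% |
| 2% | 0.5 | 0.010 | 10% | 2.4% |
| 5% | 0.5 | 0.025 | 25% | 7.3% |
| 10% | 0.5 | 0.050 | 50% | 27.6% |
| 5% | −0.5 | −0.025 | −25% | 0.07% |

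A simulation of 4000 t-tests per setting gave 2.4%, 7.0% and 26.4% for the three δ=0.5 rows. Analysing all completers as randomised gave 0.7% to 1.1%. In the last row non-watchers know more, and the sign of the bias reverses.

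**With a true effect.** Suppose watchers gain 0.1 SD and non-watchers gain nothing. The filtered estimate is 0.1 + pδ and the as-randomised estimate is 0.1(1−p). They are equal when δ = −0.1. The filtered estimate is therefore the larger one unless non-watchers would score more than 0.1 SD above watchers.

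**Cost of dropping the filter at time point 1** (2500 per arm, one-sided 0.01, power = Φ(effect/SE − 2.326)):
- No non-watchers: Φ(0.1/0.02828 − 2.326) = 88.7%.
- 5% non-watchers, filtered, 2375 versus 2500: Φ(0.1/0.02865 − 2.326) = 87.8%.
- 5% non-watchers, as randomised, effect 0.095: Φ(0.095/0.02828 − 2.326) = 84.9%.
- 10% non-watchers, as randomised, effect 0.090: 80.4%.

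**Reading the sentence.** It can mean failing either task, or doing neither. On the first reading it also conflicts with the sentence before it: a person who does not answer at time point 2 has failed at one of the time points, yet is to be kept for the immediate analysis.

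**The case against.** The strongest reply is that the rule may remove hardly anyone. If the sentence means people who do neither task, someone who skips the video but submits the questionnaire stays in. The neighbouring sentences do tie inclusion to completed surveys. Nothing shows that skipping at time point 1 is possible: the only skip wording, with its 3-second threshold, is in section {20b} and concerns the optional rewatch at the end. If the platform forces full play, the rule excludes no one who submits. Payment only on completing the whole survey also encourages adherence.

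Much of this stands as a limit on size. It does not remove the point. The rule sits under a non-adherence heading, where failing either task is the natural reading. No section says that play is forced, and the rule presupposes that non-watching can be identified.

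The planned Intervention versus Attention Placebo comparison is a partial safeguard. Both arms see an animated video of similar length, so a similar filter acts on both sides. It is not the primary comparison, but it could help to expose a selection artefact.

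A reader might infer that the primary result is certainly biased in favour of the video. The documents do not support that. The direction depends on who skips, and the last row of the table shows that it can reverse. Nor does the statement in section {15, 11c, 18b} prove that complete questionnaires from non-watchers are discarded, since it concerns incomplete datasets.

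**Conclusion.** The point holds in a limited form. On the natural reading, the plan applies an adherence-based exclusion after randomisation to one side of its primary comparison and of its medium-term comparison with the Un-exposed Arm. The bias is likely to favour the video, but this is not established.

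Its size cannot be fixed from the documents. For assumed non-watching of 2% to 10% and a 0.5 SD lower score, it is 0.01 to 0.05 SD, a tenth to a half of the target effect, with a one-sided 0.01 error of about 2.4% to 27%. With 2% and 0.25 SD it is close to negligible. The 0.01 one-sided level is taken from the sample-size section, because the analysis section states neither level nor sidedness. The loss of comparability between the arms does not depend on the direction of the bias, and the ambiguous sentence needs rewriting on any reading.

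**What to change.** Replace the last sentence of section {20c} with: the primary analysis at each time point includes every randomised participant who submitted the questionnaire at that time point, in the arm assigned, whether or not the video was watched. Align the neighbouring sentences with it. Keep a watched-video analysis, or a complier-average one, as a sensitivity analysis only, and define watching at time point 1 for that purpose.

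Report by arm the number lost between randomisation and questionnaire submission. The new wording removes only the exclusion made by the analyst. People who leave during the video are still lost from the video arms alone.

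The cost is a wording change and slight dilution. If 5% do not watch and gain nothing, time-point-1 power is about 85%, against about 88% for the filtered analysis. At 10% it is about 80%, still the planned level. At time point 2, with the plan's 20% attrition (2000 per arm), 5% non-watchers give Φ(0.095 × √1000 − 2.326) ≈ 75%, against Φ(0.1/√(1/1900 + 1/2000) − 2.326) ≈ 79% with the filter.

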## Ethics, oversight, monitoring, and dissemination

### Ethical approval and protocol amendments {24, 25}

Ethical clearance for the conduction of this study was obtained from the Stanford University Institutional Review Board (IRB) on June 7th, 2022 (protocol #65160) and a modification to this protocol was approved on Feb. 6th, 2023. Any further modifications to the study protocol will be communicated to the Stanford IRB office by the study team in a timely manner. Changes to the study protocol will not take effect before approval by the Stanford IRB.

### Informed consent {26a, 26b}

The process of obtaining informed consent will be conducted by the ProA platform. Prior to their enrolment into the study, each participant must give their informed consent, in which they will be thoroughly informed about the purpose, potential benefits, and potential risks of participating in the study. Participants will also receive contact information for both the principal investigator and the Stanford Ethics Review Board, should they have any concerns. Individuals who register on ProA are required to agree to the terms and conditions for collection and use of participant data, as well as the privacy policy of ProA.

### Confidentiality {27}

All participants will remain anonymous to the investigators for the entire duration of the trial. At no point in time, will the investigators have access to identifying information of the participants. All participants will be assigned unique ID numbers, no conclusions can be drawn to individual participants. If participants choose to contact the study team, they will be informed that their names may become visible to the study team. The study team commits to keeping all correspondence confidential.

### Access to data {29}

All investigators listed above will have access to the full and complete data set. There are no contractual agreements with any other party with respect to collection, evaluation or use of the data within this trial.

### Data monitoring and trial steering committees {21a, 21b}

This study will be overseen by a trial steering committee (TSC) made up of an independent chairperson, further members, and the study collaborators. At least two TSC meetings will be scheduled during the planning and data collection periods.

Due to the minimal risks related to this study and the very short study period, no additional data monitoring committee will be required. For the same reason, no interim analyses are planned and no specific stopping rules will be put in place.

### Adverse event reporting and harms {22, 23}

This is a minimal-risk trial. As such, we do not anticipate any adverse events. The TSC will monitor trial conduct during data collection.

### Dissemination plans {31a, 31b}

We anticipate the data collection to be completed by the end of May 2023. We seek to publish the trial findings in peer-reviewed journals and aim for presentations at scientific conferences. Authorship will be considered according to ICMJE criteria.

### Plans to give access to the full protocol, participant-level data and statistical code {31c}

This document is the full protocol. Anyone interested in other data or documentation should contact the corresponding author. The R code for the analyses will be published together with the planned publications on Github.com, as appropriate.

## Discussion

As a fully online, randomized controlled trial, this protocol describes an innovative approach to public health education in general and, more specifically, to the prevention of cardiovascular disease. Sustainable dietary sodium reduction hinges on knowledge about which foods contain high levels of sodium and how to reduce dietary sodium through behavioral shifts. As such, interventions that improve knowledge and catalyze behavioral shifts in the public offer a compelling additional tool for reducing the burden of cardiovascular disease.

While designing this trial, we considered the fact that our participant population may not be representative of the general US population. Prior research has found that users registered on ProA tend to be slightly younger and slightly more educated than US averages [12]. However, the benefits of using ProA include access to a large, geographically dispersed, adult US test population, with minimal loss to follow-up. We conclude that, since the intervention described in this protocol, if effective, would eventually be delivered via online platforms, testing it with an online community is reasonable and perhaps even advantageous.

## Trial status

Protocol version number and date: Version 1.0, 28.02.2023

Recruitment status: Not yet recruiting

Estimated study start (recruitment) date: March 1, 2023

Approximate study completion (end of recruitment): May 31, 2023

## Data Availability

Anyone interested in other data or documentation should contact the corresponding author. The R code for the analyses will be published together with the planned publications on Github.com, as appropriate.

## Appendix

Intervention video: https://youtu.be/QYqAbbifI9U

APC: https://youtu.be/LRiWQfLvQjQ

## Abbreviations

SAS: Short, animated storytelling
E-E: Entertainment-Education
ProA: Prolific Academic
APC: Attention Placebo Control
TSC: Trial Steering Committee
IRB: Institutional Review Board
